### Fidelity/quality control of the intervention

Data collection and intervention are performed by two key members of the research team, who know the research protocol well. Two operation manuals according to each hospital’s routine perinatal care process have been developed for implementing and managing the intervention. The manuals describe in detail when, where and what the project staff should do in delivering the intervention. Both of the two project staffs will be required to perform the intervention according to the operation manuals.

During the implementation of this intervention, regular online meetings will be held to report the implementation process and record problems and good experiences will also be shared to facilitate the intervention in the future.

### Strategies to enhance clinical trial compliance and retention

To maximize compliance and retention in this study, we achieved the greatest support from the hospitals. The project staff will undertake the recruitment, survey and intervention in the obstetric clinic where all early pregnant women must come to have a clinical visit with the assistance of obstetricians and nurses. If participants are found not in compliance, a telephone call, Wechat messages, or face-to-face interview will be conducted to tell the importance and the current weight gain status to let the women continue to keep compliance by using motivational interviewing. Additional strategies will include newsletters underscoring key points to do during the intervention.

### Outcomes

*The primary outcomes* of this study are the total GWG up to 32^+ 0^−35^+ 6^ weeks’ gestation and the GWG prior to the OGTT screening at 24^+ 0^−27^+ 6^ weeks’ gestation. Both will be calculated by subtracting the pre-pregnancy weight from the weight measured at the respective time points.

*The secondary outcomes *include rate of GWG per week. Weekly rate of GWG will be defined as GWG divided by the number of weeks between the date of LMP and the midterm survey (24^+ 0^ to 27^+ 6^ weeks’ gestation) and the terminal survey (32^+ 0^ to 35^+ 6^ weeks’ gestation). Weekly rate of GWG between study clinical visits at 8^+ 0^ weeks’ and 27^+ 6^ weeks’ gestation, and at 8^+ 0^ and 35^+ 6^ weeks’ gestation will be calculated by dividing the amount of weight gain between visits by the weeks of gestation between visits. The proportion of women who exceed the 2009 IOM guidelines’ weekly rate of GWG will also be assessed, and it was defined as being above the upper limit of the first trimester (2.0 kg) plus the upper limit of the weekly rate (0.33 kg/week for overweight with BMI ranging from 24.0 to 28.0 kg/m^2^, 0.27 kg/week for obesity with BMI ≥ 28 kg/m^2^), times the number of weeks in the second and third trimesters.

Other secondary outcomes include incidence of GDM diagnosed according to IADPSG criteria (FPG ≥ 5.1 mmol/L, and/or 1-h blood glucose ≥ 10.0 mmol/L, and/or 2-h blood glucose ≥ 8.5 mmol/L), rate of preeclampsia/gestational hypertension (preeclampsia was defined according to the criteria of the ACOG, i.e. systolic blood pressure of ≥ 140 mmHg or diastolic blood pressure of ≥ 90 mmHg occurring after 20 weeks of gestation in a previously normotensive woman combined with new-onset proteinuria of ≥ 0.3 g/24 h. Gestational hypertension was defined similarly but without the presence of proteinuria.), incidence of cesarean delivery, absolute/mean infant birth weight, incidence of macrosomia (with infant birth weight ≥ 4000 g), and absolute/mean Apgar scores at 1–5 min (Apgar scores at 1–5 min evaluate the baby’s heart rate, respiratory effort, muscle tone, reflex irritability, and color. Each category is scored from 0 to 2, and the total score ranges from 0 to 10. A higher Apgar score indicates that the newborn is in good health.).

In addition, pre-specified secondary outcomes also include changes of blood pressure, body fat percentage (%), fat free mass (kg), muscle mass (kg), attitude and knowledge, dietary intake, physical activity, sleep quality, quality of life, self-efficacy score, stage of change related to gestational weight control behavior, and incidence of depression and anxiety, which will be assessed from baseline (8^+ 0^−13^+ 6^ weeks) to midterm (24^+ 0^−27^+ 6^ weeks), and from baseline (8–14 weeks) to terminal (32^+ 0^−35^+ 6^ weeks). Incidence of postpartum weight retention, absolute/mean offspring weight, height, and head circumference will also be evaluated at 42 days, 6 months, and 12 months after delivery.

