### Sample size estimation

The sample size was estimated to ensure adequate power for detecting group differences in GWG at both mid- (24^+ 0^−27^+ 6^ weeks) and late-pregnancy (32^+ 0^−35^+ 6^ weeks). The anticipated differences between the two groups were 2.19 kg [13] at 32^+ 0^−35^+ 6^ gestational weeks, and 1.19 kg at 24^+ 0^−27^+ 6^ gestational week [23], the SD of the gestational weight gain would be 4 kg and 2 kg at both mid- and late-pregnancy, respectively. The rate of attrition would be 10% in each group. We aimed to recruit a total of 200 pregnant women from 2 hospitals, with 100 women per hospital. The sample size will provide 80% power with α = 0.05 to detect a mean difference of 2.19 kg in the gestational weight gain between groups after the intervention from 10^+ 0^ to 13^+ 6^ gestational weeks to 34^+ 0^~35^+ 6^ gestational weeks.

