### Randomization

The study will obtain informed consent at the baseline clinic visit at 8^+ 0^ to 13^+ 6^ weeks’ gestation. Only those women who meet the inclusion criteria, consent and complete the baseline assessment will be randomly assigned to either intervention or control group.

The 100 participants from each hospital will be randomly allocated at a 1:1 ratio to either the intervention group or the control group by the study staff, stratified by the categorical variables of age (< 30 and ≥ 30 years), pre-pregnancy BMI (< 28 and ≥ 28 kg/m^2^), and history of delivery with randomly determined block sizes of 4. Neither the staff nor the participants will be blinded to the group assignment due to the nature of the intervention program. The process of the randomization will be supervised by another study staff and recorded in a Microsoft EXCEL database.

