### Data collection

Data will be collected at clinic visits in the hospital where participants receive their usual care, and from the EMR system. Table 3 describes the study outcomes of the key three research appointments, including when and how those outcomes will be evaluated. The baseline assessment will be conducted at approximately 10 weeks’ gestation (between 8^+ 0^ and 13^+ 6^ weeks) from April to August 2024 for both the intervention and the control groups. Follow-up assessments will be conducted at approximately 26 weeks’ gestation (between 24^+ 0^ and 27^+ 6^ weeks); 34 weeks’ gestation (between 32^+ 0^ and 35^+ 6^ weeks); delivery (within 1 week after delivery); 42 days postpartum (6–8 weeks after delivery); 6 months postpartum (24–32weeks after delivery) and 12 months postpartum (48–56 weeks after delivery). Two well-trained key members of the project will be responsible for the collection, supervision, and management of data.

**Table 3 Tab3:** Outcome measurements for the HGWG-pro study

Outcomes	8^+ 0^−13^+ 6^ weeks’ gestation	24^+ 0^−27^+ 6^ weeks’ gestation		32^+ 0^−35^+ 6^ weeks’ gestation		Device (Manufacturer, model)		Methods
Anthropometric measures								
Height	√					Upright Posture Height and Weight Measuring Instrument (Shanghe Technology SH-200)		Measured to the nearest 0.5 cm at least twice without wearing shoes.
Weight	√	√		√		Upright Posture Height and Weight Measuring Instrument (Shanghe Technology SH-200)		Measured to the nearest 0.1 kg at least twice through wearing light-weight clothing without shoes.
Systolic and diastolic blood pressures	√	√		√		Fully Automatic Electronic Blood Pressure Monitor (Kentairou HBP-9020)		Measured to the nearest 1 mm Hg at least twice
Body composition	√	√		√		Bioelectrical impedance (BIA) TANITA MC-780MA		According to the standard procedure
LMP and Gestational age	√							Confirmed by ultrasounds conducted before the baseline survey clinic visit and extracted from EMR
Pre-pregnancy weight	√							Self-reported by women and extracted from EMR, if pre-pregnancy weight is not available, the earliest pregnancy weight measured before 10 weeks’ gestation will be obtained.
Behavioral measures and other measures								

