At the baseline and all follow-up visits before delivery, anthropometric measures including height, weight, systolic and diastolic blood pressures, and body composition will be collected by the trained members of the project using the same device according to the standard methods. The date of the last menstrual period (LMP) and gestational age will be confirmed by ultrasounds conducted before the baseline clinic visit and extracted from EMR. Pre-pregnancy weight will be extracted from EMR, which was collected by women’s self-report. These indicators will be used to calculate BMI for initial assessment of eligibility.

We will use questionnaires to measure women’s behaviors (food intake, dietary behavior, physical activity, sedentary behavior, average steps during the last week), and other potential mediators of the intervention effect (e.g., attitude and knowledge about EGWG, stage of readiness) for behavioral change related to gestational weight control, social support, self-efficacy, frequency of weighing at three timepoints.

The cardiometabolic markers measured in women’s laboratory tests included levels of glucose, total cholesterol, triglycerides, high-density lipoprotein (HDL), low-density lipoprotein (LDL) during routine prenatal check-ups in the early, middle and late stages of pregnancy, and results of a 75 g 2-hour oral glucose tolerance test (OGTT) will be obtained from EMR. Women’s fasting blood samples at 8^+ 0^ to 13^+ 6^, 24^+ 0^ to 30^+ 6^, and 34^+ 0^ to 37^+ 6^ weeks’ gestation will be collected to measure levels of insulin, HbA1c, et al. Urine samples at three appointments and cord blood at birth will be collected for further analyses.

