### Statistical analyses

Baseline characteristics of participants will be reported by using descriptive statistics. Statistical analyses will be based on the intention-to-treat principle, and include all women recruited with BMI ≥ 24 kg/m^2^. Multiple linear regression models/Generalized linear mixed models will be used to examine the primary and secondary outcomes at 24^+ 0^−27^+ 6^ and 32^+ 0^−35^+ 6^ gestational weeks, at delivery, at 42 d, 6 m, and 12 m after delivery, and the models will be adjusted for the clustering effect and the baseline outcome values. Chi-squared tests will be used to compare conditions on the proportion of women who exceed the 2009 IOM guidelines’ weekly rate of GWG, and other dichotomous outcomes. We will also analyze whether the outcome disparities between the intervention and control groups vary by hospitals, BMI status before pregnancy, etc. All results will be considered statistically significant as two-side *P* < 0.05. Statistical analyses will be conducted by using R software 4.4.1.

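### The primary models adjust for an undefined baseline value of weight gain; naming the gain already made at the baseline visit would remove pre-randomisation noise that other readings leave in

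*Protocol article*

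**What the plan says.** - **Entry (Randomization).** "The study will obtain informed consent at the baseline clinic visit at 8^+ 0^ to 13^+ 6^ weeks’ gestation". Allocation follows that visit: "Only those women who meet the inclusion criteria, consent and complete the baseline assessment will be randomly assigned".
- **Primary outcomes (Outcomes).** Gain up to 24+0 to 27+6 weeks and up to 32+0 to 35+6 weeks. "Both will be calculated by subtracting the pre-pregnancy weight from the weight measured at the respective time points".
- **Starting weight (Data collection).** "Pre-pregnancy weight will be extracted from EMR, which was collected by women’s self-report". Table 3 adds a fallback: "if pre-pregnancy weight is not available, the earliest pregnancy weight measured before 10 weeks’ gestation will be obtained".
- **Measured baseline weight (Data collection, Table 3).** Staff weigh each woman at the baseline visit to 0.1 kg, at least twice, on the device also used at follow-up. Under Outcomes, this weight serves the secondary weekly rate of gain between study visits.
- **Models (Statistical analyses).** Linear regression or generalised linear mixed models are planned, and "the models will be adjusted for the clustering effect and the baseline outcome values". The proportion exceeding the guideline rate, and other dichotomous outcomes, get chi-squared tests.

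**The concern.** By the time a woman is allocated, between 8 weeks and 13 weeks 6 days of the period over which her gain is counted have passed. That is 29 to 58% of the period to the mid-pregnancy visit (8/27.86 to 13.86/24) and 22 to 43% of the period to the late visit (8/35.86 to 13.86/32). The intervention cannot alter weight already gained, nor an error in the reported pre-pregnancy weight. Both still count in full in each primary outcome.

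Adjustment could remove this variation, but only with the right covariate. For blood pressure or body fat the baseline value is obvious. For gain counted from before pregnancy it could be taken as the measured baseline weight, the pre-pregnancy weight, or the difference between them. These choices do not perform alike. If the choice is left until outcome data are in hand, it becomes a post hoc decision in both primary analyses.

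**Working it through.** **The plan's own figure.** Sample size estimation states 80% power for 2.19 kg, two-sided 0.05, 200 women, 10% attrition (90 per arm analysed). With power = Φ(δ/(S√(2/n)) − 1.96), δ = 2.19 and S = 4: S√(2/90) = 0.596, 2.19/0.596 = 3.67, power 95.7%. The stated 80% is not reproduced. That is a separate matter, but it shows where the SDs of 4 kg and 2 kg come from. As worded, 4 kg belongs to mid-pregnancy and 2 kg to late pregnancy. This looks reversed, so results below are given by outcome SD rather than by visit.

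**Set-up.** Write the outcome as Y = (E − r) + L. E is true gain up to the baseline visit, r the error in reported pre-pregnancy weight, and L the gain after baseline. Observed early gain, E − r, equals measured baseline weight minus pre-pregnancy weight. Let its SD be s and the SD of Y be S.

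**Assumptions, not in the protocol.** s = 1.0 to 1.5 kg; early gain independent of L. Under independence s cannot exceed S, so for S = 2 kg it must stay below 2 kg.

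**Adjusting for early gain.** Share of variance = s²/S²; standard-error ratio = √(1 − s²/S²).

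| S (kg) | s (kg) | Share | SE ratio | SE at 90 per arm |
|---|---|---|---|---|
| 4 | 1.0 | 6% | 0.968 | 0.596 → 0.577 |
| 4 | 1.5 | 14% | 0.927 | 0.596 → 0.553 |
| 2 | 1.0 | 25% | 0.866 | 0.298 → 0.258 |
| 2 | 1.5 | 56% | 0.661 | 0.298 → 0.197 |

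A simulation at s = 1.0, 90 per arm, agrees: 0.594 to 0.574 for S = 4 and 0.298 to 0.254 for S = 2. The mean difference was the same with and without adjustment.

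**Adjusting for one weight only.** Let body weight have SD W, assumed 8 to 12 kg and unrelated to gain. The most that either weight alone can explain is R² = s⁴/((W² + s²)S²), reached when early variation is all true gain (baseline weight) or all reporting error (pre-pregnancy weight). The most favourable case, W = 8, gives:
- S = 4, s = 1.5: 5.06/(66.25 × 16) = 0.005, so the SE falls 0.2%.
- S = 2, s = 1.5: 5.06/(66.25 × 4) = 0.019, so the SE falls 1.0%.

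The corresponding reductions with early gain are 7% and 34%. Entering both weights together is equivalent to entering early gain.

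**Effect on power at 90 per arm, s = 1.0 and 1.5.**
- 2.19 kg with S = 4: 95.7% to 96.7% and 97.7%.
- 1.19 kg with S = 2: 97.9% to 99.6% and above 99.9%.
- 1.19 kg with S = 4 (the SDs as worded): 51.4% to 54.0% and 57.7%.

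**Exceedance outcome.** The limit is 2.0 kg plus 0.33 kg (overweight) or 0.27 kg (obese) per later week. Gain at baseline counts against it, and the chi-squared test takes no covariate.

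**The case against.** The strongest reply is that the adjustment is already planned. The outcome is weight minus pre-pregnancy weight, both weights are available at baseline, and so the baseline value of the outcome is naturally the gain at that visit. On that reading the primary models already contain the right covariate. The reading is plausible, but the text does not establish it, and the alternatives forfeit almost all of the benefit. It also does not reach the exceedance outcome, for which the article names a chi-squared test.

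Other points on that side stand:
- Counting from pre-pregnancy weight matches the total-gain standards in Table 1, so the outcome definition is defensible.
- The between-visit weekly rate already gives a largely sufficient sensitivity analysis from measured baseline weight.
- Eligibility relies on a self-reported weight on record, so the fallback to a weight before 10 weeks should seldom apply.

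A reader might also infer that the planning sentence concerns a different quantity, since it speaks of "gestational weight gain between groups after the intervention from 10^+ 0^ to 13^+ 6^ gestational weeks" and onward. The range of weeks most naturally gives the period of the intervention, as in Study design, and not the point from which gain is counted.

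**Conclusion.** The point holds as a modest matter of precision and clarity. With an early component of 1.0 to 1.5 kg, naming the right covariate lowers the standard error by about 3 to 7% at an outcome SD of 4 kg, and by about 13% or more at 2 kg. These figures rest on the assumed SD and on independence from later gain; a negative correlation between early and later gain would shrink them.

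Three stronger conclusions are not supported:
- **Bias.** The variation is fixed before allocation, so randomisation balances it in expectation. Only precision and chance imbalance are at stake.
- **Women already counted as exceeding at entry.** An overweight woman 5 kg up at 13+6 still has 2.0 + 0.33 × 20 − 5 = 3.6 kg left at 34 weeks. She would need more than 8.6 kg by then to be over the late limit.
- **A saving worth 16 to 64% more women.** This takes an early SD of 1.5 to 2.5 kg against a total of 4 kg only. A value of 2.5 kg (variance 6.25) cannot fit inside an outcome with SD 2 kg (variance 4).

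If the SD of 4 kg belongs to the 2.19 kg difference and 2 kg to the 1.19 kg difference, power is already about 96 to 98%, so the trial does not depend on this change.

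**What to change.** 1. Keep both primary outcomes. State that the baseline covariate in their models is measured weight at the 8+0 to 13+6 visit minus pre-pregnancy weight, using the same starting weight as the outcome.
2. For the proportion exceeding the guideline rate, replace the chi-squared test with a logistic model containing the same covariate, or a marginally standardised version giving a risk difference or ratio.
3. Label the existing between-visit weekly rate as the supporting analysis from measured baseline weight.

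Fix this before outcome data by arm are examined. It costs a few sentences of analysis wording and no extra visits, measurements or procedures. The small downside is a less simple effect measure for exceedance: an adjusted odds ratio is conditional on the covariate, which marginal standardisation avoids.

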**Methods:**

The Healthy Gestational Weight Gain program (HGWG-pro) is a two-centered randomized controlled trial that aims to evaluate the effectiveness of a multi-component intervention on promoting appropriate gestational weight gain, preventing gestational diabetes mellitus (GDM), and improving pregnancy, delivery, and neonatal outcomes among overweight or obese pregnant women aged 18 to 40 years old in China. Two maternal and child health care hospitals will be selected from the eastern region of China. Altogether 200 women with pre-pregnancy body mass index (BMI) ranging from 24 to 40 kg/m^2^ from the two hospitals will be randomized to intervention or control group. The intervention will be delivered from 10^+ 0^-13^+ 6^ weeks’ gestation to 32^+ 0^–35^+ 6^ weeks of gestation, with biweekly counseling sessions conducted either face-to-face during routine prenatal visits or via telephone, depending on the participant’s schedule. A smartphone application and wearable smart wristband will be used to assist in providing GWG related information, monitoring dietary behaviors, physical activity and weight, and providing feedback on weight and behaviors for participants. Data will be collected at 8^+ 0^-13^+ 6^, 24^+ 0^-27^+ 6^, and 32^+ 0^-35^+ 6^ weeks’ gestation, at delivery, at 42 days, 6 months and 12 months after delivery. This study has two primary outcomes: the between-group differences in gestational weight gain at 24^+ 0^-27^+ 6^ weeks’ gestation and 32^+ 0^-35^+ 6^ weeks’ gestation. The secondary outcomes will include differences between groups in weekly rate of GWG and incidence of adverse pregnancy complications and pregnancy outcomes, changes in diet, physical activity and other offspring health indicators at follow-up visits. Metabolic blood test results including indicators such as blood sugar and blood lipids will be extracted from the electronic medical record (EMR) system, indicators such as insulin and glycated hemoglobin will be measured through the collected blood samples. This trial includes a variety of process evaluation methods to evaluate the fidelity and adherence of the intervention.

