### Eligibility and recruitment

The HGWG-pro study will recruit 200 overweight or obese pregnant women from 2 hospitals, with 100 participants from each hospital. Overweight or obesity were determined based on BMI recommendations of the Group of China Obesity Task Force of the Chinese Ministry of Health (overweight: 24 ≤ BMI < 28 kg/m^2^; obese: BMI ≥ 28 kg/m^2^) [22]. Pregnant women receiving usual antenatal care at the two hospitals will be firstly identified through gestational weeks. Only those at 8–14 weeks’ gestation will be further evaluated according to the inclusion criteria: aged between 18 and 40 years, pre-pregnancy BMI between 24 and 40 kg/m^2^ based on weight self-reported and recorded in the electronic medical record (EMR), singleton pregnancy, skilled at using smartphones and WeChat (mobile application), planning to attend regular antenatal care and delivery at Weifang Maternal and Child Health Hospital of Shandong or Tongzhou Maternal and Child Health hospital of Beijing, no contraindications to physical activity according to Physical Activity Readiness Questionnaire (PAR-Q), willing to be randomized and cooperate with regular follow-up visits and sign informed consent.

Exclusion Criteria including women with pre-pregnancy hypertension, severe cardiovascular or cerebrovascular diseases, respiratory disease, hepatic or renal disease, malignant tumors, systemic lupus erythematosus, thyroid disease, severe anemia, and other chronic diseases, cervical insufficiency, multiple pregnancy, continuous vaginal bleeding, diabetes before pregnancy, special dietary needs (e.g. vegetarianism), severe psychiatric disorders, with a history of bariatric surgery or other surgical history involving important organs within 3 months; participated in other clinical trials within 6 months.

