Depression	√	√		√		Depression will be measured by 9-item Patient Health Questionnaire (PHQ-9) [34, 35]. The score ranges from 0 to 27 and the higher score indicates higher level of depression. A score greater than 4 indicates depression.		
Anxiety	√	√		√		Anxiety will be measured by Zung’s Self Rating Anxiety Scale (SAS) [36]. The score ranges from 25 to 100 and the higher score indicates higher level of anxiety. A score greater than 49 indicates anxiety.		
Social support	√					Social support will be measured by Maternity Social Support Scale (MSSS)[37], the score ranges from 5 to 30 and the higher score indicates higher level of social support.		
Self-efficacy	√	√		√		Self-efficacy will be measured by General Self-Efficacy Scale (GSES) [38, 39]. The score ranged from 10 to 40 and the higher score indicates higher level of self-efficacy.		
The stage of gestational weight control behavior	√	√		√		The investigators will use two items to assess it. “Have the participants started to adjust their diet/physical activity to control their weight during pregnancy?“, “No and I do not plan to do so in the next 6 months/No, but I am ready to start within the next 6 months/No, but I am ready to start in the next 30 days/Yes, but not regularly/Yes, I am currently controlling my weight by adjusting my diet/physical activity regularly, but it has not reached 6 months/Yes, I have been controlling my weight for more than 6 months by adjusting my diet/physical activity” choices will be provided.		
Clinical outcomes								
Gestational Diabetes Mellitus (GDM)		√				75 g 2-hour oral glucose tolerance test (OGTT), Fasting blood, Venous blood diagnosed according to International Association of Diabetes and Pregnancy Study Group (IADPSG) criteria: Fasting plasma glucose (FPG) ≥ 5.1 mmol/L, and/or 1-h blood glucose ≥ 10.0 mmol/L, and/or 2-h blood glucose ≥ 8.5 mmol/L		
Preeclampsia/ Gestational hypertension		√		√		Preeclampsia was defined according to the criteria of the American College of Obstetricians and Gynecologists (ACOG) i.e. systolic blood pressure of ≥ 140 mmHg or diastolic blood pressure of ≥ 90 mmHg occurring after 20 weeks of gestation in a previously normotensive woman combined with new-onset proteinuria of ≥ 0.3 g/24 h. Gestational hypertension was defined similarly but without the presence of proteinuria.		

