### Adverse events

The perinatal adverse outcomes, including pregnancy loss, gestational diabetes, pregnancy-induced hypertension, preeclampsia, cesarean delivery, and preterm birth (before 37 weeks) will be obtained from the EMR.

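### GDM incidence is compared in all recruited women with an unadjusted test, so women already above the trial's own fasting threshold at entry can count as incident cases and dilute the effect

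*Protocol article*

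**What the plan says.** All references are to the protocol article.

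- **Aim (Abstract, Methods).** After appropriate weight gain, the trial aims at "preventing gestational diabetes mellitus (GDM), and improving pregnancy, delivery, and neonatal outcomes".
- **Entry (Eligibility and recruitment).** "Only those at 8–14 weeks’ gestation will be further evaluated according to the inclusion criteria". The one exclusion that concerns glycaemia is in the run "diabetes before pregnancy, special dietary needs (e.g. vegetarianism". No criterion deals with raised glucose found in early pregnancy.
- **Outcome (Outcomes).** The secondary outcome is "incidence of GDM diagnosed according to IADPSG criteria (FPG ≥ 5.1 mmol/L, and/or 1-h blood glucose ≥ 10.0 mmol/L", followed by a 2-hour limit of 8.5 mmol/L. Any one value is enough. No previously normoglycaemic condition is attached.
- **Test (Table 3).** GDM is ticked once, at the 24+0 to 27+6 week visit, and assessed by "75 g 2-hour oral glucose tolerance test (OGTT), Fasting blood, Venous blood diagnosed according to" the same criteria. There is no baseline GDM assessment.
- **Early glucose (Data collection).** Glucose is extracted from the EMR as measured "during routine prenatal check-ups in the early, middle and late stages of pregnancy". Separately, fasting blood is drawn at 8+0 to 13+6 weeks for insulin, HbA1c and other unnamed measures.
- **Adverse events.** Gestational diabetes is among the perinatal outcomes that "will be obtained from the EMR".
- **Analysis (Statistical analyses).** The intention-to-treat analyses "include all women recruited with BMI ≥ 24 kg/m^2". Chi-squared tests are assigned to the dichotomous outcomes.

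**The concern.** Incidence is the occurrence of new cases among people free of the condition at the start. Here nothing separates women below the trial's fasting limit at entry from those already at or above it. The preeclampsia definition in the same Outcomes section does make this separation: onset must be after 20 weeks in a woman who was normotensive before, and pre-pregnancy hypertension is an exclusion. GDM has no matching condition.

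The intervention starts at 10+0 to 13+6 weeks. If some women are above the limit before it starts, remain so at the OGTT and do not respond, they add the same expected number of cases to each arm. The risk ratio moves towards 1 and power falls. The reported incidence then mixes status at entry with new onset, which matters because prevention is a stated aim. The chi-squared test cannot use the early glucose that the trial collects, so it neither corrects a chance imbalance nor gains precision.

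**Working it through.** The article gives no event rate, power or sample size for GDM, so there is no stated figure to reproduce. The arithmetic below is an illustration.

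**Inputs from the article.** 200 women, 1:1 allocation, 10% attrition: 200/2 × 0.90 = 90 evaluable per arm. Two-sided α = 0.05.

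**Assumptions, not in the article.**
- Among women below the limit at entry, GDM risk is 30% (control) v 15% (intervention), a true RR of 0.50.
- A share f of women enters at or above the limit, equal in both arms in expectation: 10% or 20%.
- A proportion q of those women is positive at the mid-pregnancy OGTT: half or all.
- The intervention has no effect in them.

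**Formulas.**
- Control risk = f·q + (1 − f)·0.30
- Intervention risk = f·q + (1 − f)·0.15
- Share of control cases already above the limit at entry = f·q / control risk
- Power: normal approximation for two proportions, pooled variance under the null, 90 per arm

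**Worked case, f = 0.10, q = 1.** Control 0.10 + 0.27 = 0.370. Intervention 0.10 + 0.135 = 0.235. RR = 0.235/0.370 = 0.64. Share = 0.10/0.370 = 27%.

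| f | q | Control | Intervention | Observed RR | Power, all women | Share of control cases |
|---|---|---|---|---|---|---|
| 0 | – | 0.300 | 0.150 | 0.50 | 67.6% | 0% |
| 10% | 0.5 | 0.320 | 0.185 | 0.58 | 55.0% | 16% |
| 10% | 1 | 0.370 | 0.235 | 0.64 | 50.5% | 27% |
| 20% | 0.5 | 0.340 | 0.220 | 0.65 | 43.3% | 29% |
| 20% | 1 | 0.440 | 0.320 | 0.73 | 38.1% | 45% |

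Restricting to women below the limit leaves 90 × 0.9 = 81 or 90 × 0.8 = 72 per arm, with power of 63.0% or 57.9%.

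**Sensitivity to the assumed risks** (q from half to all):
- Control risk 20%, true RR 0.50: observed RR 0.61 to 0.68 at f = 10%, and 0.69 to 0.78 at f = 20%.
- Control risk 30%, true RR 0.70: observed RR 0.75 to 0.78 at f = 10%, and 0.79 to 0.84 at f = 20%.

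**Sensitivity to the no-effect assumption.** If the intervention halves the risk in women above the limit too, then at f = 0.10, q = 1 the intervention risk is 0.05 + 0.135 = 0.185 and the RR is 0.185/0.370 = 0.50. There is then no dilution.

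**Type I error.** With no effect in any woman, both arms have the same expected risk whatever f and q are, so the test keeps its 5% level.

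**The case against.** **Early glucose is not itself the event.** A reader might infer that a woman with 5.1 mmol/L at booking is automatically an incident case. The article does not support that. Table 3 fixes one OGTT in mid-pregnancy, the Outcomes section places the OGTT screening at 24+0 to 27+6 weeks, and 1-hour and 2-hour limits apply only to such a test. She counts only if she is positive then. This stands, and makes the q = 1 rows the extreme.

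**EMR does not mean any time.** A reader might also see a contradiction between the Adverse events section and Table 3. The former names a data source, and Data collection says OGTT results come from that same source. The two are compatible; the Adverse events wording merely gives no time window.

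**Unpreventable is an assumption.** The article does not say that a raised early value persists or cannot respond to lifestyle change. The dilution, and the power advantage of restriction, both depend on this assumption.

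**The comparison is valid.** GDM at the mid-pregnancy OGTT in all randomised women is a legitimate intention-to-treat contrast. Saying that the trial cannot address prevention would go too far. Dropping women from the main analysis would be a debatable trade against that principle.

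**It could wait for an analysis plan.** A supplementary analysis could. But the article itself fixes the incidence label, the population and the unadjusted test. Its mention of adjustment for baseline outcome values does not help here, because GDM has no baseline value and chi-squared is assigned to dichotomous outcomes.

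**Conclusion.** The point holds as dilution and imprecise labelling of one secondary outcome. Nothing in the article prevents women above the trial's own fasting limit at entry from being enrolled and counted as incident GDM if the later OGTT is positive, and the planned test ignores the glucose information collected. The arms are not biased against each other, type I error is intact and the weight-gain primaries are unaffected.

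The size cannot be determined from the article, which does not say how many such women there will be. In the illustration, a true RR of 0.50 is seen as 0.58 to 0.64 (10% above the limit) or 0.65 to 0.73 (20%), and power falls from 67.6% to between 55.0% and 38.1%. These figures rest on the assumed rates and on no effect in women above the limit. They shrink as fewer of those women test positive or more of them benefit.

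**What to change.** 1. In Outcomes, state that the GDM outcome is the OGTT result at 24+0 to 27+6 weeks, as in Table 3, and align the Adverse events wording with it.
2. Keep all randomised women as the main GDM analysis, but replace the chi-squared test with a regression adjusted for fasting glucose measured before randomisation. Use the baseline fasting sample at 8+0 to 13+6 weeks, or the early EMR value if it is confirmed to be fasting and to precede allocation. The article says neither of the EMR value.
3. Add a supplementary analysis restricted to women below the trial's own fasting limit at entry. Because the restriction uses a pre-randomisation value, it preserves the randomised comparison, and it is the analysis that estimates incidence.
4. Report by arm the number of women at or above the limit at entry.

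Adjustment adds precision and deals with chance imbalance. It does not by itself turn the all-women result into incidence, so steps 2 and 3 are both needed.

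Cost: some wording, slightly more analysis work and a smaller denominator in the supplementary analysis. Glucose is not named among the assays on the baseline fasting sample, so one assay may have to be added if the EMR value is unsuitable. Enrolment and care do not change.
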